### Criteria for discontinuation of tests

Serious safety issues occurred during the trial, and the investigator believed that the safety of the subjects may be compromised.It was observed that the therapeutic effect of the experimental intervention was found to be relatively poor or potentially ineffective, suggesting limited clinical value.Major errors were found in the clinical trial protocol, or significant deviations occurred during the trial implementation, making it challenging to assess the trial’s purpose.The supervision and administration department requested suspension.

### Interventions

Patients eligible for the study will be assigned to one of the different groups and will receive one of the following two treatments:

A 5.2 g YQFM injection is diluted into 250 mL of 0.9% sodium chloride injection and administered intravenously once daily for 10 days.The placebo injection, which is a 10 mL 0.9% sodium chloride injection, is diluted into 250 mL 0.9% sodium chloride injection and administered through intravenous drip once daily for 10 days.

All enrolled patients will receive guideline-directed medical therapy in accordance with the Chinese guidelines for the diagnosis and treatment of acute ischemic stroke in 2018 [30]. The treatment measures mainly include lipid-lowering, blood sugar-lowering, and antiplatelet aggregation therapies, and it is required that each hospital maintains the same drug varieties when using medications with similar efficacy.On this basis, the test group received YiQiFuMai lyophilized injection and the control group received 0.9% sodium chloride injection for 10 days. The treatment assignment is illustrated in Fig. 1.

Administration of other TCM or Chinese patent medicines, similar in function and indications with the investigational medicine, and of all traditional Chinese medicine injections will be prohibited during the treatment period. Moreover, during the study period, the use of Chinese herbal decoctions (granules) and other traditional Chinese patent medicines for the treatment of acute ischemic stroke will be prohibited.

If an SAE occurs, a participant or their legally authorized representative requests withdrawal from the study, or a participant does not comply with the prescribed intervention, the investigational drug will be discontinued. Any reasons for discontinuing the intervention will be recorded.

### Primary outcome

The main efficacy measure will be the percentage of patients with the ability to engage in “relatively independent” daily living (Modified Rankin Scale ≤ 2, which is defined as relative independence) at D90.

### Secondary outcomes

Secondary outcomes will include the following: the percentage of early neurological deterioration (defined as an increase of 2 or more points in the NIHSS score at D3 compared to baseline), the degree of neurological deficiency (measured by the change in the NIHSS scale between baseline and D10), patient self-reported outcome (measured by the change in the PRO scale between baseline and D10), change in Traditional Chinese medicine syndrome (evaluated using a stroke syndrome elements scale at baseline and D10), degree of disability (evaluated by the distribution of mRS scores at D30 and D90), proportion of patients capable of performing daily living activities (evaluated by BI scale scores at D30 and D90), mental status assessment (evaluated using MMSE scores at D90), recurrence rate of cerebrovascular events and stroke-related mortality within 90 days of onset, and incidence of important vascular events within 90 days.

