**Methods:**

This trial is a prospective, multicenter, randomized, double-blind, placebo-controlled, superiority trial aimed at evaluating the efficacy and safety of YQFM in reducing the disability rate in patients with acute hypoperfusion stroke within 90 days. We will recruit 480 patients with AIS within 48 h of symptom onset from 24 hospitals, who have large atherosclerosis, systolic pressure ≤ 155 mmHg, and an NIHSS score of 4–18. Eligible patients will be randomly assigned to receive either YQFM or 0.9% NaCl injection once daily for 10 days and will be followed up until the 90th day after stroke onset.The primary outcome will be the proportion of patients with mRS ≤ 2 at 90 days after patient recruitment. Secondary outcomes will include the proportion of early neurological deterioration at 7 days, patient self-reported outcomes and the syndrome score at 10 days, MMSE scale and BI scale at 90 days.During the trial, adverse events will be recorded. These data will be analyzed according to the predetermined statistical analysis plan.

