### Data analysis

The missing data are processed by multiple interpolation. If the primary efficacy index is missing, the previous result is carried forward according to the intentionality analysis.If there is a valid value carried forward after randomization, the last observation is used for carry-over.

The main efficacy measure (the percentage of patients with mRS ≤ 2 ) will be compared and analyzed using the chi-squared test. The statistician will perform covariate adjusted analyses and covariate unadjusted analyses. Subgroup analyses will include sex, age, systolic blood pressure, and the baseline NIHSS score.

For dichotomous outcomes, such as the percentage of BI ≥ 90, distribution of mRS scores, proportion of early neurological deterioration, and recurrence rate of stroke, we will use the chi-squared test or Fisher’s exact test to compare the distribution of patients between the two groups.Logistic regression is utilized to estimate the 95% CI. For continuous variables, including neurological function scores, MMSE scores, PRO scale, cerebral blood flow, such as changes from baseline to treatment endpoints, Student’s t-test or Wilcoxon rank-sum test is employed to analyze the differences between the two groups.Survival data will be estimated using the Kaplan-Meier method, survival curves will be plotted, and efficacy will be evaluated using log-rank tests.

According to the safety set data, statisticians compare and analyze the differences in the incidence of adverse events, major adverse events, and liver and kidney dysfunction, as well as routine blood and urine tests between the two groups. For most safety data, Cox proportional-hazards models are used to estimate the hazard ratios between the two treatment groups.

When 50% of the subjects have completed the study, an interim analysis will be conducted. The continuation or suspension of the study is determined according to the analysis results. If the analysis results indicate that valid results cannot be obtained, the study will be terminated immediately. The study will continue if data analysis suggests that efficacy may be achieved at the end of the study.

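### The PRO secondary outcome is a change from baseline to D10, but the printed visit schedule assesses PRO only at Day 10, so definition and schedule must be reconciled

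*Protocol article*

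**What the plan says.** Three places in the protocol article describe the PRO outcome, and a fourth schedules it.

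- **Secondary outcomes** gives the definition: "patient self-reported outcome (measured by the change in the PRO scale between baseline and D10".
- **Data analysis** puts PRO among the continuous variables compared by t-test or Wilcoxon rank-sum test: "MMSE scores, PRO scale, cerebral blood flow, such as changes from baseline to treatment endpoints".
- **Abstract, Methods** shortens it to "patient self-reported outcomes and the syndrome score at 10 days", without mentioning a change.
- **Appendix C, the visit flow chart**, has seven visit columns (Screening, Day 1, Day 3, Day 7 ± 1, Day 10 ± 1, Day 30 ± 3, Day 90 ± 7). The PRO row has one tick, under Day 10 ± 1.

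**The concern.** The definition requires a baseline value and the schedule does not provide one. The visit chart is the part of a protocol that tells sites when to apply each instrument, so the disagreement bears on what data will exist.

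If the chart describes actual practice, the stated outcome cannot be formed. Recruitment began in November 2023, and a patient's own report of their state in the first days of a stroke cannot be obtained months later. If the chart is merely incomplete, the data exist and only the document is wrong.

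Either way the question should be settled while treatment groups are still masked. Otherwise the choice between a change score and a D10 score may be made with results in view.

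**Working it through.** The plan gives no figure to reproduce here. The check is a comparison of each scale outcome's definition with its scheduled assessments.

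**Step 1: read the chart row by row.** Each scale row was split into its 8 cells (procedure name plus 7 visits) and the ticks were matched to the columns.

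| Scale | Quantity in Secondary outcomes | Ticks in Appendix C | Obtainable as defined? |
|---|---|---|---|
| NIHSS | change, baseline to D10 | Screening, Days 3, 7, 10 | yes |
| Syndrome evaluation scale | baseline and D10 | Days 1, 3, 7, 10 | yes |
| **PRO** | **change, baseline to D10** | **Day 10 only** | **no** |
| BI | D30 and D90 | Days 1, 30, 90 | yes |
| MMSE | D90 | Days 1, 90 | yes |
| mRS | D30 and D90 | Screening, Days 1, 30, 90 | yes |

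**Step 2: rule out a table-reading error.** The neighbouring rows agree with their own definitions, so the columns have not slipped. A slip would not help in any case: the PRO row holds one tick in total, and one assessment in any column cannot give a difference between two times.

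**Step 3: count.** Assessments needed for a change score: 2. Assessments scheduled: 1. Of the three scales that Secondary outcomes measures from baseline (NIHSS, PRO, syndrome scale), PRO alone has no scheduled baseline. BI and MMSE, which are defined at follow-up visits only, do have a Day 1 assessment.

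**Step 4: what can still be estimated.** Let Y0 be the baseline score, Y1 the D10 score and T the treatment group.

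- *With a baseline.* The model Y1 − Y0 = a + τT + bY0 rearranges to Y1 = a + τT + (b + 1)Y0. The treatment effect τ is identical, so ANCOVA on the D10 score still addresses the change outcome.
- *Without a baseline.* Randomisation makes a comparison of mean Y1 between groups valid, provided missing D10 values are handled adequately.
- *Precision.* Assume equal variance at both times and correlation ρ between Y0 and Y1. Relative to the unadjusted D10 comparison, the variance of the treatment effect is 1 − ρ² with ANCOVA and 2(1 − ρ) with the raw change score. ANCOVA is never worse in large samples. The raw change beats D10 alone only when 2(1 − ρ) < 1, that is, when ρ > 1/2. The article gives no ρ, so the loss cannot be put as a number.

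**The case against.** The strongest reply is that Appendix C is a condensed table and the missing tick may be no more than a printing omission. The same chart is incomplete elsewhere. The medication record and adverse event rows have no Day 1 tick, although Day 1 is the first column of the treatment phase and dosing is daily. Stool tests named under Safety outcomes do not appear in the laboratory row. The flowchart, the patient timeline figure and the supplement are not available here, and any of them might show a Day 1 PRO. This objection stands, and it limits the conclusion to what follows if the printed schedule is followed.

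Three other inferences are tempting and unsupported:

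- *The abstract shows that a D10-only outcome was intended.* It does not. The same phrase shortens the syndrome score in the same way, and that outcome uses both a baseline and a D10 assessment, with a scheduled Day 1 value.
- *The outcome is undefined.* It is defined clearly under Secondary outcomes; the schedule fails to match it. The Data analysis wording is illustrative and covers several variables, so it agrees with that definition but does not fix it independently.
- *Some centres will add a baseline on their own and so select the analysed patients.* Nothing in the article suggests this.

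It is also fair to say that the reach is small: one item among the secondary outcomes, with a valid randomised comparison available even in the worst case.

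**Conclusion.** The definition and the printed schedule contradict each other, and following the plan as written yields no PRO change score. The size is one scheduled assessment against the two required.

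A reader might infer that the endpoint is already lost for all 480 patients and beyond repair. The documents do not support that unconditionally. It would be true only if sites collect PRO exactly as Appendix C prints it, and the article cannot show whether they do.

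The primary outcome (mRS ≤ 2 at D90) and the sample size calculation make no use of PRO and are unaffected. Even if the only error is an omitted tick, the article needs correcting.

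**What to change.** Before the first level of unblinding, and before anyone sees PRO results by group:

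1. **Check the eCRF** to see whether a Day 1 PRO is collected. This comes first, because a stated secondary outcome should not be redefined during recruitment if the data for it exist.
2. **If it is collected:** add the Day 1 tick to the PRO row of Appendix C. Specify ANCOVA of the D10 PRO score with baseline PRO as covariate. The cost is a schedule correction and a sentence in the analysis text.
3. **If it is not collected:** restate the outcome in Secondary outcomes and in Data analysis as the between-group difference in PRO score at D10. Adjust for baseline variables that are scheduled, such as NIHSS, and for centre, which is the randomisation stratum. Handle missing D10 scores by the planned multiple imputation (the article writes interpolation). With a single PRO assessment there is no earlier PRO value to inform the imputation, so the model must draw on the other scheduled measures. The cost is some precision compared with a baseline-adjusted PRO. Record the change and its date, with a statement that it was made under masking.

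Neither route requires a change to the primary analysis or to the number of patients.

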### Exploratory outcomes

In the intervention and control groups, one-third of the patients from hospitals compliant with brain MRI standards will be observed the change of index of cerebral blood stream and microcirculation under DWI and arterial spin labeling test for brain MRI. Proteomics will be employed to search for differential gene and protein expression.

### Safety outcomes

Safety evaluations include adverse events (AEs), which are any medical events that occur after the subject has received the investigational drug. These events can be manifested as symptoms, signs, diseases, or laboratory abnormalities. It is important to note that AEs may not be causally related to the investigational drug. Additionally, serious adverse events (SAEs) are also evaluated. SAEs include severe outcomes such as death, intracranial hemorrhage, progressive stroke, vascular events.

Laboratory studies (including a complete blood count, routine urine measures, routine stool measures, and measures of liver function, kidney function), vital signs, and an electrocardiogram will be conducted. The causality of adverse events will be determined with reference to the WHO Collaboration Center for International Drug Monitoring, using the criteria of the Uppsala Monitoring Center.

### Monitoring and quality control

Before enrolling the subjects, on-site centralized training, video training, and other forms of training will be conducted for the researchers in each sub-center included in the implementation plan. Each sub-center will issue a researcher folder, which will be saved by a designated person.

A unique login ID will be used by the clinical research coordinator to collect information at each visit point and record data in a timely, accurate, complete, and clear manner in an electronic case report form (eCRF), which will be signed by the researcher. All medical center researchers will make reasonable efforts to follow up patients throughout the entire study period.

A third-party professional monitoring agency will undertake the monitoring tasks of our research group. This agency will regularly monitor all study data and conduct quality control of the study data. Additionally, a clinical research associate will regularly monitor the research data and researcher folder through both online monitoring using an Electronic Data Acquisition System and on-site monitoring.

In this study, inspectors were selected from personnel not directly involved in the experiment. They formulated the inspection process and completed the on-site inspection. At the beginning, middle, and end of the experiment, one third of the research centers were inspected respectively. The inspection focused on the group leader unit, the unit with the fastest and most enrolled subjects, the unit with the first cooperation, and the unit with abnormal data.At the end of the trial, all study centers were inspected at least once.

A third party statistical agency will complete the statistical analysis of the data. Researchers, statistical analysts, monitors, and data managers will design a data verification plan. The data administrator will draft a data audit report and lock the database, which will be carried out jointly by the research team leader and statistical analysts.

### Management of adverse events and adverse reactions

We will record any AEs that occur during the course of the study and will assess whether they are related to the investigational drug, properly handled, and tracked until they are resolved, or until the condition stabilizes. AEs and unexpected events will be reported in a timely manner to the Data Security and Monitoring Board, Ethics Committee, and Chief Investigator.

If AEs occur during the trial, the investigator may take necessary treatment measures according to the condition to ensure the safety of the subjects, record them, and decide whether the subjects’ participation should be terminated in the trial. In case of serious adverse events, the subjects should be withdrawn from the clinical trial, and appropriate measures for the subjects should be taken immediately. The insurance for the enrolled subjects will be covered by this study, ensuring the protection of their rights.

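### The adverse-event section takes patients with an SAE out of the trial, while Interventions only stops the drug; followed as written, survivors lose their D90 mRS and later events

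*Protocol article*

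**What the plan says.** The protocol article states two consequences of an SAE.

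- **Management of adverse events and adverse reactions:** "In case of serious adverse events, the subjects should be withdrawn from the clinical trial". The sentence before it, on adverse events in general, leaves it to the investigator whether the patient's participation ends.
- **Interventions:** an SAE is one of three triggers after which "the investigational drug will be discontinued". Another trigger in the same sentence is that "a participant or their legally authorized representative requests withdrawal from the study".

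Other sections bear on what follows:

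- **Safety outcomes:** "SAEs include severe outcomes such as death, intracranial hemorrhage, progressive stroke, vascular events".
- **Primary outcome:** the proportion with mRS ≤ 2 at D90.
- **Secondary outcomes:** these include "recurrence rate of cerebrovascular events and stroke-related mortality within 90 days of onset", and important vascular events over the same 90 days.
- **Monitoring and quality control:** "All medical center researchers will make reasonable efforts to follow up patients throughout the entire study period".
- **Data analysis:** multiple imputation is named for missing data in general. For the primary outcome, however, "If the primary efficacy index is missing, the previous result is carried forward according to the intentionality analysis", and "If there is a valid value carried forward after randomization, the last observation is used for carry-over".
- **Appendix C (visit flow chart):** mRS is scheduled at screening, Day 1, Day 30 and Day 90 only.

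**The concern.** Stopping a drug and leaving a trial are different things, and the Interventions sentence itself treats them as different. A site that follows the adverse-event section literally will not bring an SAE survivor back at D30 or D90.

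That would make the primary outcome missing for a reason tied to the outcome, because haemorrhage, progression and vascular events are what move a patient across the mRS 2/3 boundary. It would also end the search for later strokes, vascular events and deaths in those survivors, so they would be informatively censored in the planned Kaplan-Meier, log-rank and Cox analyses. The event or death that triggers withdrawal is still recorded. What is at risk is everything after it in patients who survive.

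**Working it through.** **Step 1: what withdrawal can mean.** Study drug is given for 10 days and outcomes run to day 90. Days after the last dose: 90 − 10 = 80, or 80/90 = 89% of the period. An SAE in that window leaves no drug to stop, so the withdrawal instruction either means leaving follow-up or has no content. This is a count of calendar days and says nothing about when SAEs occur. Within the section, the preceding sentence is about ending participation, which supports the first meaning.

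**Step 2: what the analysis would use instead of the D90 mRS.**

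- *SAE after D30:* the last post-randomisation mRS is the D30 value, which predates the event. A patient with mRS ≤ 2 at D30 who is then disabled is scored a success.
- *SAE before D30:* only the screening and Day 1 values exist. They may already exceed 2, or may not qualify as post-randomisation values. The direction of the effect is uncertain.

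**Step 3: size, for SAEs after D30.** The article gives no figure to reproduce on this point: no SAE rate and no D30 mRS distribution. The only planning figure needed is the assumed effect, 76.5% − 65% = 11.5 points (Sample size calculations). The rest is assumption:

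- *r* = share of an arm surviving a post-D30 SAE and withdrawn (T = YQFM, C = control)
- *a* = share of those patients with mRS ≤ 2 at D30
- *b* = share of them truly at mRS ≤ 2 at D90, set to 0.20

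Carry-forward overstates an arm's success proportion by r × (a − b). With *a* and *b* the same in both arms:

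bias in the difference = (r_T − r_C) × (a − b)

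| r_T | r_C | a | b | Calculation | Bias (points) |
|---|---|---|---|---|---|
| 0.10 | 0.05 | 0.60 | 0.20 | 0.05 × 0.40 | +2.0 |
| 0.06 | 0.03 | 0.60 | 0.20 | 0.03 × 0.40 | +1.2 |
| 0.10 | 0.05 | 0.40 | 0.20 | 0.05 × 0.20 | +1.0 |
| 0.06 | 0.03 | 0.40 | 0.20 | 0.03 × 0.20 | +0.6 |
| 0.05 | 0.05 | 0.60 | 0.20 | 0 × 0.40 | 0 |
| 0.05 | 0.10 | 0.60 | 0.20 | −0.05 × 0.40 | −2.0 |

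With equal rates the difference is unbiased, but each arm's proportion is still overstated: at 5%, by 0.05 × 0.40 = 2.0 points.

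**Step 4: patients affected.** With 240 per arm, 0.05 × 240 = 12 and 0.10 × 240 = 24 patients lack an observed D90 mRS. These counts hold only if the assumed rate refers to survivors, since a death has a known outcome. Check on the first row: 24 × 0.40 − 12 × 0.40 = 9.6 − 4.8 = 4.8 net misclassified patients, and 4.8/240 = 2.0 points.

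**The case against.** The best opposing case is that loss of follow-up is inferred. No section says outright that the D30 and D90 visits stop. The Interventions rule only stops the drug. The monitoring section asks sites to try to follow patients to the end of the study, with no exception for SAEs. Adverse events are followed until they resolve or settle, and Appendix C records them at D30 and D90. The Subject withdrawal section does not list SAEs. The English is loose throughout, and the withdrawal sentence goes on to require immediate measures for the patient, so it may be only an acute instruction to stop treatment. A fuller protocol may settle the matter.

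Part of this stands. The lost visits are a consequence of the wording, and some sites may well keep following patients. But the general follow-up statement does not mention patients withdrawn for an SAE, tracking an event until it settles is not a D90 visit, and silence in the withdrawal section does not cancel an explicit instruction elsewhere. Nor is this a detail left out of a condensed article: two stated rules disagree. A later analysis plan cannot recover visits that were not made, and different readings across 24 hospitals would themselves be a problem.

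The objections to the magnitude also stand in part. Every rate is assumed, and the 2.0-point figure needs both a doubled SAE rate on YQFM and a 40-point fall in good outcome between D30 and D90. Carry-forward would affect any missing D90 mRS; the withdrawal rule matters because it generates missing values in patients selected by a bad event.

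**Conclusion.** The concern holds and should be fixed; confidence is medium, because the loss of visits follows from the wording and is not stated. The natural reading of the adverse-event section is exit from the trial, in conflict with Interventions. Applied as written, it removes outcome data for outcome-related reasons, and for SAEs after D30 it substitutes a pre-event mRS.

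In the unequal-rate scenarios the treatment difference is distorted by 0.6 to 2.0 points. The sign depends on which arm has more SAEs: a higher rate on YQFM flatters the drug, and a higher rate on control understates a true benefit. None of the scenarios reverses an 11.5-point effect. The effect of SAEs before D30, and of missed later events and deaths on the 90-day analyses, cannot be sized from the article.

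**What to change.** Amend the sentence in Management of adverse events and adverse reactions to agree with Interventions. Suggested content: an SAE may end study drug but does not end follow-up. After an SAE, or after an investigator's decision to withdraw the patient under Subject withdrawal, the patient remains in follow-up unless consent is withdrawn. D30 and D90 mRS, vital status and vascular events are still collected and are analysed in the randomised arm. This takes no position on when study drug should be stopped.

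The cost is one protocol sentence and a memo to the 24 sites; the D30 and D90 visits are already scheduled. Recruitment began in November 2023, with initial completion expected in December 2025, so the change helps only patients whose follow-up is not yet over when the memo arrives.
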